### Outcomes

2.8

#### Primary outcome

2.8.1

The 30-day follow-up window was selected to encompass the main perioperative recovery period, during which most clinically apparent infections related to the index surgery are expected to be identified, while preserving temporal proximity to the transient intraoperative lactate exposure. With longer follow-up, infections may be increasingly influenced by post-discharge exposures, rehospitalization, subsequent invasive procedures, and additional treatments, thereby weakening their relationship with TWA lactate exposure. Although the specific mechanisms differ, all these infections share common pathways of immunosuppression and impaired host defense. The types of postoperative infections include sepsis, pulmonary infection, surgical site infection, mediastinitis, and infective endocarditis. The postoperative follow-up time is shown in Table 1.

#### Secondary outcomes

2.8.2

Each component of the composite postoperative infection outcome will be analyzed separately as an exploratory secondary outcome, including sepsis, pulmonary infection, surgical site infection, mediastinitis, and infective endocarditis.

Postoperative 24-hour SIRS score: SIRS refers to the systemic inflammatory response syndrome caused by any pathogenic factor acting on the body. SIRS is diagnosed when two or more of the following criteria are met: (1) body temperature >38 °C or <36 °C; (2) heart rate >90 beats/min; (3) respiratory rate >20 breaths/min or PaCO₂ < 32 mmHg; (4) white blood cell count >12 × 10⁹/L or <4 × 10⁹/L, or immature granulocytes >10%.

Postoperative 24-hour lactate clearance: it will be calculated as follows: [(lactate at the end of surgery−lactate at 24 h after surgery)/lactate at the end of surgery] × 100%.

Mortality: patients who die within 30 days, 3 months, 6 months, and 1 year postoperatively.

Acute kidney injury (AKI): defined according to KDIGO AKI criteria (36): an increase in serum creatinine ≥0.3 mg/dL (≥26.5 μmol/L) within 48 h postoperatively, or an increase to 1.5 times the baseline within 7 days after surgery. In this study, AKI diagnosis relies entirely on elevated creatinine levels. Postoperative sCr peak is defined as the highest recorded creatinine level within 7 days after surgery (37).

Liver injury: postoperative liver injury is defined as elevation of liver enzymes ≥3 times and hyperbilirubinemia (>3 mg/dL or 51 μmol/L) within 3 days after surgery (38, 39).

ICU length of stay: defined as the time from admission to the cardiovascular ICU postoperatively until transfer to the general cardiovascular ward.

Mechanical ventilation duration: defined as the time from admission to the cardiovascular ICU after surgery until extubation in the ICU when extubation criteria are met.

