#### Exclusion criteria

2.2.2

History of previous cardiac surgery requiring sternotomy and/or CPB; 2. Emergency surgery; 3. Presence of any type of preoperative infection (e.g., preoperative pneumonia, infective endocarditis); 4. Severe hepatic or renal dysfunction (e.g., jaundice, coagulation disorders, hepatic encephalopathy, serum creatinine >442 μmol/L, blood urea nitrogen >20 mmol/L, or requiring dialysis); 5. Preexisting immunodeficiency disorders (e.g., HIV infection, use of immunosuppressive drugs, autoimmune diseases).

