### Assessment of postoperative infection

2.5

Postoperative infections will be evaluated by an independent, professionally trained review panel, including attending or higher–level cardiac surgeons, ICU physicians, and infectious disease specialists. All adjudicators will remain blinded to patients' lactate exposure group assignment and TWA lactate values. Postoperative infections to be recorded include sepsis, pulmonary infection, surgical site infection, mediastinitis, and endocarditis. The frequency of postoperative infection assessment is shown in Table 1.

**Table 1 T1:** Schedule of data collection and measurement time points.

Outcome measure Time		Visit 1	Visit 2	Visit 3	Visit 4	Visit 5	Visit 6	Visit 7	Visit 8
		Presurgery	During operation	Postoperative day 1	Postoperative day 2	Postoperative day 3	Postoperative day 7	Postoperative day 14	Postoperative day 30
Enrollment	Eligibility screening	×							
	Informed consent	×							
	Demographic characteristics	×							
	Baseline measures	×							
	Preoperative comorbidities	×							
Intraoperative	Surgery-related variables		×						
	physiological and anesthesia-related		×						
Postoperative	laboratory indices			×					
	SIRS score			×					
	GCS score			×	×	×	×	×	×
	Sequential Organ Failure Assessment Score			×	×	×	×	×	×
	Postoperative infection			×	×	×	×	×	×
	Acute kidney injury				×		×		
	Liver injury					×			
	ICU length of stay			×	×	×	×	×	×
	Mechanical ventilation duration			×	×	×	×	×	×
	Postoperative Adverse Events	Safety outcomes will be assessed from admission through 30 days post-surgery							

SIRS score, systemic inflammatory response syndrome score; GCS score, glasgow coma scale score.

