Postoperative data: Postoperative 24 h: arterial blood gas analysis, hemoglobin (g/L), platelet count (10⁹/L), lymphocyte count (10⁹/L), neutrophil count (10⁹/L), 24-hour lactate clearance (%), 24-hour SIRS score, postoperative complications, PCT (ng/mL), CRP (mg/L). Duration of mechanical ventilation (hours), ICU length of stay (hours). Creatinine (μmol/L) within 7 days postoperatively, and alanine aminotransferase (ALT, U/L) and aspartate aminotransferase (AST, U/L) levels within 3 days postoperatively.

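### AKI is coded from creatinine alone, so a patient who starts renal replacement before any qualifying creatinine is recorded, and never reaches one afterwards, counts as having no AKI

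*Protocol article*

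**What the plan says.** All places are in the protocol article.

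- **Section 2.8.2, Secondary outcomes.** AKI is met by either of two rises: "an increase in serum creatinine ≥0.3 mg/dL (≥26.5 μmol/L) within 48 h postoperatively, or an increase to 1.5 times the baseline within 7 days". The rule is then made exclusive: "In this study, AKI diagnosis relies entirely on elevated creatinine levels". The peak is also defined: "Postoperative sCr peak is defined as the highest recorded creatinine level within 7 days after surgery".
- **Section 2.11.1, Data collection.** The one postoperative renal item named is "Creatinine (μmol/L) within 7 days postoperatively". Postoperative renal replacement is not named. The list does contain a general entry for postoperative complications.
- **Section 2.5, Table 1.** AKI appears to be marked at two visits, postoperative days 2 and 7. The SOFA score is marked on days 1, 2, 3, 7, 14 and 30, and adverse events run to day 30.
- **Section 2.2.2, Exclusion criteria.** Patients with severe renal dysfunction, including those "or requiring dialysis", are not enrolled. Any replacement begun after surgery is therefore new.
- **Section 2.9, Statistical analysis.** P values for secondary outcomes are Holm–Bonferroni adjusted.

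**The concern.** The creatinine criterion works as long as creatinine is free to rise. Renal replacement removes creatinine, so the marker is altered by the treatment given for the condition it is meant to detect. If replacement begins before a qualifying value has been recorded, and no later value reaches either limit, the patient is entered as having no AKI despite severe renal failure.

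Where replacement was started for renal failure, the error runs one way: it can hide cases but cannot create them. Section 2.10 does not repair it. Creatinine measured during replacement is an observed value, so neither the imputation nor the complete-case analysis touches it. Nor can a later analysis document simply add a replacement clause, because it would contradict the exclusive wording in section 2.8.2.

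At stake are the AKI risk in each lactate group and the lactate–AKI odds ratio.

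**Working it through.** **1. The plan's own figures.** The plan gives no AKI or replacement rate, so there is no AKI figure to reproduce. The sample size in section 2.3 rests on infection only: 10.4% in the normal-lactate group and an odds ratio (OR) of 2.75.

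- Odds in the high-lactate group: 2.75 × 0.104/0.896 = 0.319, so the risk is 0.319/1.319 = 24.2%.
- A two-proportion calculation with pooled variance, two-sided α 0.05 and power 0.90 gives 156 per group (312 in total), which is the stated figure.

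AKI does not enter this calculation, so changing its definition leaves the sample size as it is.

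**2. Who is miscoded.** Three things must all hold: replacement starts within the AKI window; no qualifying creatinine is recorded before it starts; and none is recorded afterwards. A rise of 26.5 μmol/L within 48 h is a low bar, and 1.5 times baseline within 7 days is a second route. The group is therefore narrow. It would be wider if creatinine is drawn mainly at the two apparent AKI visits.

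**3. How many (rates assumed).** Replacement in 2–5% of 312 patients, with 20–40% of those missed:

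- low end: 312 × 0.02 × 0.20 = 1.2
- high end: 312 × 0.05 × 0.40 = 6.2

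This is about 1 to 6 patients over both groups together.

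**4. Effect on the odds ratio (rates assumed).** Let the true AKI risks be 20% (low lactate) and 30% (high lactate). The true OR is (0.30/0.70)/(0.20/0.80) = 1.71. Treat every replacement patient as a true AKI case, and subtract from each risk the replacement rate times the share missed. For replacement of 1% vs 5% with half missed:

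- low lactate: 0.20 − 0.005 = 0.195
- high lactate: 0.30 − 0.025 = 0.275
- observed OR: (0.275/0.725)/(0.195/0.805) = 0.3793/0.2422 = 1.57

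| Replacement, low vs high lactate | 10% missed | 25% missed | 50% missed | all missed |
|---|---|---|---|---|
| 1% vs 2% | 1.71 | 1.70 | 1.69 | 1.66 |
| 1% vs 5% | 1.68 | 1.64 | 1.57 | 1.42 |
| 2% vs 8% | 1.67 | 1.61 | 1.50 | 1.28 |

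With true risks of 30% vs 45% (OR 1.91) and half missed, the three rows give 1.88, 1.77 and 1.70.

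**5. The direction depends on the assumption.** If replacement were 2% in both groups with half missed, the risks would read 19% and 29%. The OR would be (0.29/0.71)/(0.19/0.81) = 0.4085/0.2346 = 1.74, slightly away from the null. For small shares, the OR falls only if the share missed with high lactate exceeds that with low lactate by a factor of about (0.30 × 0.70)/(0.20 × 0.80) = 0.21/0.16 = 1.31. The documents have no figure that settles this.

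**The case against.** The case for leaving the definition alone has five parts.

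- **It is an open, prespecified choice.** The plan states the restriction plainly and nothing else in it disagrees. This stands: the point is an improvement to a design choice, not a contradiction.
- **Replacement may be recorded after all.** Complications and adverse events are collected, SOFA has a renal component scored on six days, and the full CRF is not shown. A reader might infer that the study does not collect replacement at all. The documents support only that it is not named as a data item. Wherever it is recorded, the exclusive wording still bars it from counting as AKI.
- **Few patients are affected.** This stands, for the reasons in step 2 of the working.
- **The high-lactate group need not be hit harder.** A reader might infer that the missed cases cluster there, because section 2.6 lists renal dysfunction as a mediator of lactate, and might then quote an absolute understatement of the exposed AKI risk. The mediator is an assumption of the causal diagram, not a rate. Any such figure needs an invented placement of the missed patients and a fixed exposed group of 156, whereas exposure is observed and group sizes are not set in advance.
- **The remedy can err the other way.** If replacement is begun for a non-renal reason such as acidosis, and that goes with high lactate, counting every start as AKI could inflate the odds ratio. This stands, and it is why the creatinine-only result must be kept alongside.

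**Conclusion.** The gap holds and is minor. The definition has no provision for patients whose creatinine is lowered by renal replacement, so some of the most severe renal cases can be coded as event-free. On assumed rates this concerns about 1 to 6 of 312 patients. In the illustration with replacement of 1% vs 5%, the odds ratio moves from 1.71 to between 1.68 and 1.57 when 10–50% of replacement cases are missed. Larger shifts need replacement to be common with high lactate and usually missed. Every AKI and replacement rate used here is an assumption. A bias toward the null is plausible but not shown.

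A reader might also infer that analyses of peak creatinine are distorted. Section 2.8.2 defines the peak, but neither it nor section 2.9 describes an analysis of the peak as an outcome, so there is nothing to change there.

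AKI is one of several Holm-adjusted secondary outcomes. The primary infection outcome, its analysis and the sample size are untouched.

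**What to change.** These changes concern how the outcome is coded. They are not a rule on when to treat.

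1. In section 2.8.2, replace the exclusive sentence with: AKI is present if the creatinine criteria are met or if renal replacement therapy is newly started within 7 days after surgery.
2. In section 2.11.1 and on the CRF, add renal replacement: yes/no, start date, indication.
3. Repeat the AKI analysis with the creatinine-only definition as a sensitivity analysis. Replacement started for non-renal reasons could itself be more common with high lactate, and a material difference between the two results should be reported with the recorded indications.

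The cost is one clause, three fields from the ICU chart and one repeated analysis. As a sensitivity analysis it adds no test to the Holm family. The change should be fixed before outcome data by lactate group are seen, because reclassifying these patients later would be a post hoc change of outcome.

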### Statistical analysis

2.9

Data with a normal distribution will be expressed as mean ± standard deviation (SD), non-normally distributed data as median and interquartile range (IQR), and categorical variables as frequency (n) and percentage (%). Baseline data will be compared using two-sample t-tests, Mann–Whitney U tests, or chi-square tests. Univariate logistic regression analysis will be used to evaluate the association between TWA lactate, covariates, and postoperative infection, calculating odds ratios and 95% confidence intervals (95% CI). The following are the primary analyses: according to the DAG (Figure 4), confounders that are common causes of both TWA lactate and postoperative infection will be adjusted for, whereas mediators and colliders on the causal pathway will not be adjusted. In the model, TWA lactate will be analyzed as both a categorical variable and a continuous variable. Multivariable logistic regression will be employed to assess the risk association between TWA lactate and postoperative infection, reporting adjusted odds ratios (aOR) and 95% CI. For the continuous analysis, aOR will be reported per 0.5 mmol/L increase, per 1.0 mmol/L increase, and per 1-standard deviation increase in TWA lactate. For the categorical analysis, TWA lactate will be dichotomized according to the prespecified cutoff of 2.0 mmol/L. The median of tertiles will be used as a quasi-continuous variable to analyze the linear trend between TWA lactate and postoperative infection risk. Restricted cubic spline regression will be applied to explore the potential nonlinear relationship between TWA lactate and postoperative infection. Threshold analysis will be performed using segmented regression, and the likelihood ratio test will be applied to compare the goodness-of-fit between linear and nonlinear models to identify the optimal model. Based on the determined threshold, an adjusted segmented linear regression model will be constructed to estimate aOR and 95% CI before and after the threshold. The following are the secondary analyses: prespecified subgroup analyses will be conducted according to key characteristics, including age, sex, preoperative comorbidities, and surgery type, and interaction effects will be evaluated. To assess robustness, we will perform sensitivity analyses using lactate load and peak lactate during CPB, and repeat the statistical analyses. To control the error of type I due to multiple comparisons, *P* values for secondary outcomes and prespecified subgroup interaction tests will be adjusted using the Holm–Bonferroni method. All statistical tests are two-sided, and *P* < 0.05 is considered statistically significant.

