Currently, studies on the association between lactate levels and the risk of postoperative infection in cardiac surgery are limited and the evidence is insufficient. Studies on lactate and cardiac surgical outcomes have primarily focused on organ dysfunction, mortality, intensive care unit (ICU) length of stay, and postoperative mechanical ventilation time (16, 17). In the field of infection research, investigations of lactate have mainly centered on its role in assessing sepsis severity and prognosis (18). Moreover, a retrospective study of adult cardiac surgery found that there was no significant difference in the incidence of postoperative infection between the high lactate group and the low lactate group (19). However, another more recent retrospective study found that patients with postoperative pneumonia had significantly higher perioperative lactate levels than those without pneumonia (20). Therefore, in this particular population of cardiovascular surgery patients, the lactate levels during surgery and the incidence of various types of postoperative infections, such as pulmonary infection, surgical site or mediastinal infection, and infective endocarditis, still lack large-scale prospective cohort studies.

In patients undergoing cardiac surgery with CPB, evaluating the predictive value of lactate exposure during CPB as an early warning indicator for postoperative infection may help address current evidence gaps. It can provide a scientific basis for perioperative management, early infection identification, and individualized prevention strategies, thereby reducing complication rates and healthcare burdens. Therefore, the relationship and predictive value between lactate and postoperative infection warrant validation through larger, prospective cohort studies, underscoring the clear clinical and scientific significance of the present research.

This study is a single-center, prospective cohort study designed to investigate the association between time-weighted average (TWA) lactate levels during CPB and postoperative infection in patients undergoing cardiac surgery. The null hypothesis of this study is that the time-weighted average lactate level during CPB is not associated with postoperative infection in patients undergoing cardiac surgery with CPB.

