### Sample size calculation

2.3

Previous studies have reported that the incidence of postoperative infection after cardiovascular surgery is approximately 10.4%–15.5% (21–23). To obtain a conservative sample size estimate and avoid overestimating the expected event rate, we used the lowest reported incidence of 10.4% as the baseline infection rate in the normal lactate group. The same study that reported this baseline incidence also reported an odds ratio (OR) of 2.75 for postoperative infection in the high-lactate group compared with the normal-lactate group (21). With a two-sided *α* of 0.05 and a power of 0.9, the required sample size per group was estimated to be 156 using PASS 2021 software (NCSS, LLC, Kaysville, UT, USA), resulting in a total sample size of 312. Considering a 10% loss to follow-up, at least 173 participants per group are needed, for a total of 346 participants.

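### Dichotomous, continuous and tertile-trend analyses of TWA lactate are all labelled primary at P<0.05, with no deciding test named and no multiplicity rule covering them

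*Protocol article*

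**What the plan says.** The null hypothesis, at the end of the Introduction, is that "the time-weighted average lactate level during CPB is not associated with postoperative infection". It does not say how TWA lactate is coded.

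Section 2.9 (Statistical analysis) opens a block labelled as the primary analyses, which runs until the secondary analyses are announced. On the exposure it says "In the model, TWA lactate will be analyzed as both a categorical variable and a continuous variable". The categorical form is the split at 2.0 mmol/L. The continuous form is reported per 0.5 mmol/L, per 1.0 mmol/L and per standard deviation. Then: "The median of tertiles will be used as a quasi-continuous variable to analyze the linear trend". A restricted cubic spline and a segmented threshold model, the latter with a likelihood ratio comparison of linear and nonlinear fits, follow in the same block.

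On error control, P values for "secondary outcomes and prespecified subgroup interaction tests will be adjusted using the" Holm–Bonferroni method, and the section closes with "All statistical tests are two-sided, and *P* < 0.05 is considered statistically significant".

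Section 2.3 (Sample size calculation) describes one comparison of high with normal lactate: "With a two-sided *α* of 0.05 and a power of 0.9", 156 per group.

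**The concern.** Three analyses address the same null of no association (dichotomy, continuous, tertile trend). All carry the primary label and all are judged at two-sided 0.05. The article states a multiplicity rule, but that rule covers the secondary outcomes and subgroup interactions and leaves the primary family out.

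Two things are at stake. First, the conclusion that TWA lactate is associated with infection, which the Discussion ties to a possible role as a risk-stratification tool, could rest on whichever coding reaches significance, with a chance of error above 5%. Second, if the codings disagree (for example, the dichotomy is not significant but the trend is), nothing fixed in advance says which result counts. Section 2.10 adds to the ambiguity: it says the primary analysis, in the singular, will be repeated on complete cases, although section 2.9 lists several.

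**Working it through.** **1. What the sample size allows for.** Inputs from section 2.3: "we used the lowest reported incidence of 10.4% as the baseline infection rate in the normal lactate group"; odds ratio 2.75; two-sided α 0.05; power 0.90; equal groups.

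- Odds at 10.4%: 0.104/0.896 = 0.1161. Times 2.75 = 0.3192. Rate in the high-lactate group: 0.3192/1.3192 = 0.242.
- Mean rate p̄ = (0.104 + 0.242)/2 = 0.173.
- n per group = [1.960·√(2p̄(1−p̄)) + 1.282·√(p₁(1−p₁) + p₂(1−p₂))]² / (p₂ − p₁)²
- = [1.960 × 0.5349 + 1.282 × 0.5259]² / 0.1380² = 1.722² / 0.01903 ≈ 155.9, so 156.

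This reproduces the stated 156 per group (312 in total). The calculation therefore assumes exactly one two-group test at 0.05.

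**2. How many separate tests of the null there are.** The three continuous scalings are one test with one P value, so they add no multiplicity. The tests of association are three: dichotomy, continuous and trend. The spline and segmented models are set aside here because they address the shape of the relationship.

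**3. Upper reference if the tests were independent.** Two tests: 1 − 0.95² = 9.75%. Three tests: 1 − 0.95³ = 14.3%. These tests share the same data and are strongly correlated, so the true figures are lower.

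**4. Simulation under no association.** N = 312, infection rate 17% for everyone (close to the mean rate in step 1), unadjusted logistic models, 2,500 data sets per scenario. The article gives no distribution for TWA lactate, so a lognormal is assumed, with the median and log-SD varied.

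| Median, log-SD | Dichotomy alone | Continuous alone | Trend alone | Dichotomy or continuous | Any of the three |
|---|---|---|---|---|---|
| 2.0, 0.4 | 4.9% | 5.1% | 5.0% | 7.8% | 9.5% |
| 2.0, 0.6 | 5.3% | 4.8% | 4.9% | 8.6% | 10.5% |
| 1.6, 0.4 | 4.9% | 5.0% | 4.8% | 7.7% | 9.4% |
| 2.6, 0.4 | 4.0% | 4.4% | 4.6% | 7.5% | 9.4% |

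Monte Carlo standard error near 8%: √(0.08 × 0.92/2500) ≈ 0.5 percentage points. A separate run with 15.5% infections, likelihood ratio tests and 1,500 data sets gave 6.8% for dichotomy or continuous. Hence about 7–9% for the two main codings and about 10% with the trend.

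**5. Cost of keeping two primary tests.** With Bonferroni at 0.05/2 = 0.025, the critical value is 2.241.

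- Power at 156 per group: Φ[(√156 × 0.1380 − 2.241 × 0.5349)/0.5259] = Φ(1.00) ≈ 84%.
- For 90% power: [2.241 × 0.5349 + 1.282 × 0.5259]² / 0.01903 = 1.873² / 0.01903 ≈ 184.3, so 185 per group. With 10% loss, 185/0.9 = 205.6, so 206 per group and 412 in total.

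Holm is less strict than Bonferroni, so power for the dichotomous test would lie between 84% and 90%.

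**The case against.** The strongest reply is that the dichotomy already leads. Section 2.1 defines the exposure group by the 2.0 mmol/L cutoff, section 2.3 sizes the study on high versus normal lactate, and section 2.4 prespecifies the cutoff and presents the continuous form as an addition for later analyses. An analysis plan that is not shown could make the ranking explicit. This stands in part: the design does point to the dichotomy. But section 2.9, the operative text, gives both codings the same standing, and the article itself sets the multiplicity rule and the primary label. The gap lies in what is stated, not in what is left to another document.

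A second reply is that no sentence says any significant result rejects the null. That is correct. The error rates above hold only under that reading, which the text neither adopts nor rules out.

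A reader might go further in two ways that the documents do not support:

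- **Counting the spline and segmented models as further tests of the null.** In the first simulation, adding them raises the rate to about 14–15% and then 25–27%. But the spline is worded as exploring nonlinearity and the likelihood ratio test as comparing model fit, so both concern shape. The highest figure also assumes a naive 1-df reference for a searched breakpoint, which the article does not specify.
- **Saying the 5% on which the study was sized is lost.** It is not: the dichotomous test alone rejects in 4.0–5.3% of null data sets.

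**Conclusion.** The point holds in a limited form. Three analyses of association are called primary, each at two-sided 0.05, none is named as decisive, and the stated Holm–Bonferroni rule does not reach them, although the sample size provides for one dichotomous comparison. If any significant result is taken as rejecting the null, the false-positive rate is about 7–9% for the dichotomous and continuous codings and about 10% with the trend.

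These figures rest on an assumed lognormal TWA lactate, and the main simulation is without covariate adjustment. They varied little over the distributions tried. The excess is real but modest. The lack of a prespecified reading for discordant results does not depend on the simulation at all.

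**What to change.** In section 2.9, before results are seen:

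- Name the adjusted odds ratio for TWA ≥2.0 versus <2.0 mmol/L, the contrast that sized the study, as the single primary test at two-sided 0.05.
- Make continuous TWA and the tertile trend supportive, reported as estimates with confidence intervals.
- Place the spline and segmented threshold models under exploratory analyses, since they address the shape of the relationship.

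This takes one or two sentences. The planned 346 participants are unchanged and every analysis is still reported. It also settles what the primary analysis in section 2.10 refers to.

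If both codings must stay primary, apply Holm across the two and restate the power in section 2.3: about 84% at 156 per group under Bonferroni, or 185 per group (412 in total with 10% loss) to keep 90%.

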### Covariates

2.6

To ensure appropriate confounder control and strengthen inference, a directed acyclic graph (DAG) and temporal sequence diagrams for variables were constructed based on prior clinical knowledge and published evidence (Figures 3, 4). These diagrams clarify the assumed causal pathways linking intraoperative TWA lactate to postoperative infection. The DAG identified the following minimal sufficient adjustment set: age, sex, BMI, lifestyles (including smoking and alcohol consumption), comorbidities, preoperative lactate, anesthesia factors, surgery and CPB factors (including surgery type, operation duration, CPB time, aortic cross-clamp time, and intraoperative body temperature). These variables are common causes of elevated lactate during cardiopulmonary bypass and of postoperative infection risk. Mediators include hepatic and renal dysfunction, lactate clearance, inflammatory response, and immunosuppression. ICU length of stay, hospital length of stay, time to extubation, and mortality are considered collider variables.

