#### Preoperative comorbidities

2.6.2

Hypertension (systolic BP ≥140 mmHg or diastolic BP ≥90 mmHg or taking antihypertensive drugs, yes/no), diabetes (fasting glucose ≥7.0 mmol/L, 2-hour postprandial glucose ≥11.1 mmol/L, random glucose ≥11.1 mmol/L, or taking antidiabetic drugs, yes/no), arrhythmias (including atrial arrhythmia, ventricular arrhythmia, atrioventricular block, yes/no), history of cerebrovascular disease (including cerebral infarction or hemorrhage, yes/no), hypoproteinemia (serum total protein <60 g/L or serum albumin <35 g/L, yes/no), pulmonary comorbidities (including chronic obstructive pulmonary disease, asthma, interstitial lung disease, pulmonary edema, yes/no), anemia (adult male <120 g/L, adult female <110 g/L, yes/no) and obesity (BMI ≥30 kg/m^2^, yes/no).

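### With roughly 45–54 expected infections on about 24 parameters, the adjusted logistic model is likely to overstate a real lactate association; prespecify a Firth fit

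*Protocol article*

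**What the plan says.** The protocol article fixes three things that have to be read together.

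- **Model.** Section 2.9 (Statistical analysis): "Multivariable logistic regression will be employed to assess the risk association between TWA lactate and postoperative infection". It reports adjusted odds ratios with 95% intervals and adjusts for the DAG confounders. No penalised or bias-reduced fit is named.
- **Adjustment set.** Section 2.6 (Covariates): "The DAG identified the following minimal sufficient adjustment set: age, sex, BMI, lifestyles (including smoking and alcohol consumption), comorbidities, preoperative lactate, anesthesia factors", followed by surgery type, three durations and temperature. Section 2.6.2 defines eight yes/no comorbidities. The last of these begins "obesity (BMI ≥30 kg/m" and is therefore a cut of BMI, which is already in the set.
- **Size.** Section 2.3 (Sample size calculation): "we used the lowest reported incidence of 10.4% as the baseline infection rate in the normal lactate group"; "an odds ratio (OR) of 2.75 for postoperative infection in the high-lactate group"; "With a two-sided *α* of 0.05 and a power of 0.9"; 156 per group, "resulting in a total sample size of 312". This is an unadjusted comparison of two proportions, and the section does not set the expected number of infections against the size of the adjusted model.

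**The concern.** In logistic regression, the information for a coefficient depends on the number of events more than on the number of patients. With few events per parameter, ordinary maximum-likelihood estimates are biased away from an odds ratio of 1, and a rare covariate category may contain no events at all, which sends its coefficient to infinity.

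The adjusted odds ratio is the headline result, and the Discussion proposes lactate as a risk-stratification and intervention tool if an association is found. An exaggerated odds ratio would carry straight into that use. Section 2.9 also places spline and segmented models among the primary analyses, and these add parameters to the same events.

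**Working it through.** **1. The plan's own figure.** With 10.4% in the normal-lactate group and an odds ratio of 2.75, the odds at high lactate are 2.75 × 0.104/0.896 = 0.319, so the rate is 0.319/1.319 = 24.2%. The pooled two-proportion formula (two-sided 0.05, power 0.90, no continuity correction) gives 156 per group, as stated.

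**2. Expected infections among 312 evaluable patients.**

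- Equal groups: 156 × 0.104 + 156 × 0.242 = 54.
- 30% exposed (an assumption, since the plan does not say what share will exceed the cutoff): 312 × (0.7 × 0.104 + 0.3 × 0.242) = 45.
- If 15.5%, the top of the quoted range, were the overall rate: 312 × 0.155 = 48.
- If 10.4% were the overall rate: 312 × 0.104 = 32.

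**3. Parameters in the adjusted model.**

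| Item | Parameters |
|---|---|
| TWA lactate | 1 |
| Age, sex, BMI, smoking, alcohol | 5 |
| Comorbidities, entered singly | 8 |
| Preoperative lactate | 1 |
| Anesthesia factors (assumed one term) | 1 |
| Surgery type, five categories in 2.6.4 | 4 |
| Three durations and temperature | 4 |
| **Total** | **24** |

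One comorbidity score in place of eight indicators gives 24 − 8 + 1 = 17. The six surgery categories in section 2.11.1 would add one.

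**4. Infections per parameter.** 45/24 = 1.9 and 54/24 = 2.25; 45/17 = 2.6 and 54/17 = 3.2.

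**5. Effect on the estimate.** Simulation used 2,000 data sets per setting and a correctly specified model, with 312 patients and a true conditional odds ratio of 2.75 unless noted. The document gives no covariate prevalences or correlations, so these are assumptions: comorbidities at 8–50% or, in a rarer set, 5–50%; surgery types at 5–40%; correlated durations; about half of patients exposed.

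| Setting | Events | Parameters | Estimated ÷ true log OR | Mean OR, ordinary ML | Mean OR, Firth |
|---|---|---|---|---|---|
| Base prevalences | 54 | 24 | 1.11 | 3.09 | 2.69 |
| Rarer comorbidities | 54 | 24 | 1.14 | 3.16 | 2.75 |
| Base prevalences | 48 | 24 | 1.15 | 3.21 | 2.76 |
| Rarer comorbidities | 48 | 24 | 1.13 | 3.15 | 2.71 |
| Covariates without effect | 54 | 24 | 1.10 | 3.05 | not run |
| One comorbidity count | 54 | 17 | 1.07 | 2.96 | not run |
| All 346 analysed | 60 | 24 | 1.12 | 3.10 | not run |
| True OR 1.5 | 54 | 24 | 1.11 | 1.57 | not run |
| True OR 1 | 32 | 24 | – | 1.03 | not run |

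Mean ORs are geometric means. Separate runs under other assumptions at 45–54 events gave median odds ratios of about 3.0–3.15 with ordinary ML and 2.68–2.76 with Firth. With a true odds ratio of 1, the rejection rate was 6.4% at a nominal 5%.

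**6. Size relative to noise.** At 54 events the bias is 0.114 to 0.139 × ln 2.75 (1.012) = 0.115 to 0.141 on the log scale, against a standard deviation of the estimate of 0.44 to 0.46. That is about 0.26 to 0.31 standard deviations. Coverage of the ordinary 95% interval was about 94%.

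**7. Separation.** At 54 events some coefficient diverged in 9% of data sets with base prevalences and 22% with rarer comorbidities. Other assumptions at design-level events gave about 1–5%. Dropping or merging rare categories (20 parameters) brought it to 0.2% while the mean OR stayed at 3.09. The lactate coefficient itself did not diverge in any data set at 48 or 54 events.

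**The case against.** Several points on the other side are sound.

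- **The estimator is not named.** Section 2.9 does not say maximum likelihood, and Firth's method is itself a logistic regression. A separate analysis plan could specify it. However, the adjustment set, the model class and the sample size are all fixed in this document, and the difficulty lies in their combination. Ordinary maximum likelihood is the plain reading.
- **The count of 24 is a reading.** Section 2.6 names comorbidities and anesthesia factors only as groups. Collapsing comorbidities to one score reduces the inflation to about 7% at 54 events but does not remove it.
- **The bias is smaller than the sampling error**, as step 6 shows, and interval coverage suffers little.

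A reader might also infer stronger claims that the documents do not support.

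- **32 infections together with an odds ratio of 2.75.** This pairing gives inflation near 20% and frequent separation. But section 2.3 places 10.4% in the normal-lactate group, so any positive association lifts the total above 32. That count applies only if 10.4% is the overall rate, for example with no association.
- **That overstatement is built in whatever the truth.** With no association there is no material bias, and the null hypothesis is tested close to its nominal level.
- **That separation will often spoil the primary result.** Its frequency depends on prevalences the document does not give, and it falls on rare covariate categories.
- **That the rare infection components will be fitted with the full model.** Section 2.8.2 calls them exploratory and does not say so.
- **That some durations can be dropped to save parameters.** Section 2.6 places all three in the minimal sufficient set, so removing one would contradict the DAG and risk confounding.

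**Conclusion.** The point holds in moderate form. On the plan's own assumptions the primary adjusted model has about 2 infections per parameter, or up to about 3 if comorbidities are one score. Ordinary maximum likelihood would then inflate the log odds ratio of a real association by roughly 7–15%, so that 2.75 is estimated at about 3.0–3.2. The direction was the same in every simulated setting with a true association.

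The size rests on assumed covariate prevalences and correlations, on one anesthesia term, on how comorbidities are coded, and on an exposed share between 30% and 50%. The harm is an exaggerated effect if the study's hypothesis is true, not a false positive if it is not. It deserves correction because it is predictable and inexpensive to remove; it does not invalidate the study.

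**What to change.** In section 2.9, state that the primary adjusted model will be fitted by Firth's penalised logistic regression with profile penalised-likelihood intervals, and that the ordinary maximum-likelihood fit will be reported as a sensitivity analysis. Where section 2.10 leads to multiple imputation, fit the penalised model within each imputed data set and say how the profile intervals are combined, since Rubin's rules pool estimates and variances rather than profile limits.

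Enter BMI as a continuous covariate, omit the obesity indicator that duplicates it, and say whether the other comorbidities enter singly or as a score. Keep all other DAG confounders, including the three durations. If the sparse infection components are modelled, use the same penalised method.

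The cost is a few lines of text and standard software, with no extra patients. The downside is slight shrinkage and intervals that readers know less well.
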